## Abstract

**Background:**

Gastric cancer is the third most common cause of cancer-related deaths and has the fifth highest incidence worldwide, especially in eastern Asia, central and Eastern Europe, and South America. Currently, surgery is the only curative treatment for gastric cancer; however, there is an increasing trend toward laparoscopic radical gastrectomy. Early oral feeding (EOF) has been shown to benefit clinical outcomes compared with open gastrectomy under conditions of enhanced recovery after surgery. There are a lack of guidelines and evidence for the safety and feasibility of EOF in patients undergoing laparoscopic radical gastrectomy. Thus, a prospective randomized trial is warranted.

**Methods/design:**

The EOF after total laparoscopic radical gastrectomy (SOFTLY) study is a single-center, parallel-arm, non-inferiority randomized controlled trial which will enroll 200 patients who are pathologically diagnosed with gastric cancer and undergo laparoscopic radical gastrectomy. The primary endpoint, incidence of anastomotic leakage, is based on 1.9% in the control group in the CLASS-01 study. The patients will be randomized (1:1) into two groups: the EOF group will receive a clear liquid diet on post-operative day 1 (POD1) and the delayed oral feeding (DOF) group will receive a clear liquid diet on post-operative day 4 (POD4). The demographic and pathologic characteristics will be recorded. Total and oral nutritional intake, general data, total serum protein, serum albumin, blood glucose, and temperature will be recorded before surgery and at the time of hospitalization. Adverse events will also be recorded. The occurrence of post-operative fistulas, including anastomotic leakage, will be recorded as the main severe post-operative adverse event and represent the primary endpoint.

**Discussion:**

The safety and feasibility of EOF after gastrectomy has not been established. The SOFTLY trial will be the first randomized controlled trial involving total laparoscopic radical gastrectomy, in which the EOF group (POD1) will be compared with the DOF group (POD4). The results of the SOFTLY trial will provide data on the safety and feasibility of EOF after total laparoscopic radical gastrectomy.

**Trial registration:**

Chinese Clinical Trial Registry, ChiCTR-IOR-15007660. Registered on 28 December 2015. The study has full ethical and institutional approval.

**Electronic supplementary material:**

The online version of this article (10.1186/s13063-019-3493-2) contains supplementary material, which is available to authorized users.

## Background

The 2014 World Cancer Report, published by the WHO [1, 2], indicated that gastric cancer was the fifth most common malignancy (951,600 cases; 6.8% of total) and the third leading cause of cancer deaths in 2012 worldwide (723,100 deaths; 8.8% of total). Gastric resection is the main treatment approach by which to prolong the survival of patients with gastric cancer [3].

It has been reported that approximately 30% of cancer patients are malnourished, most of whom are upper gastrointestinal cancer patients [4]. In 1980, the Eastern Cooperative Oncology Group (ECOG) reported that the prevalence of malnutrition among gastric cancer patients was as high as 87% [5].

The disease itself and drug treatment, as well as the effect of surgery on the gastrointestinal tract and metabolic system, are all potential contributors to post-operative malnutrition, which could lead to post-operative infections, prolong the post-operative length of stay (LOS), and increase morbidity and mortality [6–8].

Nutritional support is crucial after gastric surgery. Due to the protection of the anastomotic site and potential transient ileus [9], a fasting period with only parenteral nutrition after gastric surgery until bowel function is clinically detectable is routine [10]. Nevertheless, parenteral nutrition as the only nutritional route has greater nutritional and immunological disadvantages than enteral nutritional support [11, 12].

The European Society for Parenteral and Enteral Nutrition (ESPEN) and Enhanced Recovery After Surgery Society guidelines recommend early initiation of normal food intake or enteral feeding after gastrointestinal surgery (grade A) and enteral tube feeding (e.g., a needle catheter jejunostomy or nasojejunal tube) when oral intake is not possible. Limited data are available regarding immediate oral intake in patients with anastomoses undergoing gastrectomies [13, 14]. Early oral feeding (EOF) as a natural nutritional route after gastric surgery has been recently reported in randomized controlled trials (RCTs) and a meta-analysis, and delayed oral feeding serves as the control [15–19].

These studies have shown an improvement with EOF directly after gastric surgery; specifically, recovery of bowel function was more rapid, the post-operative LOS was shorter, and the surgical and general complication rates were less. Few studies have evaluated EOF in patients with gastric cancer undergoing laparoscopic radical gastrectomy, including total and subtotal gastrectomies [15–18].

Previous studies [15–17] on EOF after open gastrectomy led us to hypothesize that patients with gastric cancer undergoing totally laparoscopic radical gastrectomies treated with EOF have similar or lower anastomotic leakage rates, fewer complications, and a more rapid recovery when compared with delayed oral feeding. Some evidence indicates that EOF as part of early recovery after surgery (ERAS) is feasible and safe after gastric cancer surgery [15, 20] and is associated with a shorter hospitalization and time to gas passage. The surgical procedure and digestive reconstruction are the main differences between open and laparoscopic radical gastrectomy [21] (especially total laparoscopic radical gastrectomy (TLRG)). In the current study, patients with gastric cancer in the EOF group will begin a clear liquid diet on post-operative day (POD)1, while patients in the delayed oral feeding (DOF) group will begin a clear liquid diet on POD4; both groups will have no volume limitations. Only patients undergoing totally laparoscopic gastrectomy will be included. Therefore, we have designed a safety and feasibility RCT to verify the hypothesis. The results may serve as the basis for further study of EOF after TLRG.

The objective of the current study is to assess whether or not EOF after TLRG will increase the anastomotic leakage rate compared with DOF. We seek to determine whether or not a clear liquid diet on POD1 increases the anastomotic leakage rate or could lead to better functional recovery following TLRG compared with oral feeding on POD4. The study design will determine the safety and feasibility of EOF after laparoscopic radical gastrectomy and provide supplementary evidence of ERAS guidelines after TLRG.

## Methods/design

SOFTLY is a non-inferiority, single-center, parallel-arm RCT in which 200 patients will be randomly assigned to one of two different times post-operative oral feeding will be initiated after TLRG. The trial flow chart is shown in Fig. 1.

**Fig. 1 Fig1:**
[figure not shown]
Study design flow chart

The SOFTLY trial will test the hypothesis that EOF, which will be initiated on POD1, is not inferior to DOF on POD4 for patients undergoing TLRG in terms of anastomotic leakage rate.

A complete checklist of items according to SPIRIT 2013 [22] is provided in Additional file 1.

### Ethics approval

The study procedures and informed consent form have been approved by the independent Ethics Committee of Xijing Hospital in Shaanxi province, China. Information about any adverse events (AEs) will be reported to the Ethics Committee until reaching a stable situation. The Ethics Committee has the duty to periodically evaluate the progress of this trial.

### Randomization procedure

Participants who meet the eligibility criteria will be randomly assigned to either the EOF group or the DOF group with a 1:1 ratio. The sequence of randomization has been generated by a biostatistician who is not involved in this trial with SAS software version 9.2 (SAS Institute, Cary, NC, USA). The randomization list has been sealed in sequentially numbered opaque envelopes, which have been stored in a double-locked cabinet. Randomization is implemented by a research assistant who is not involved in recruitment. After random assignment, the envelopes will again be stored separately. Because the participants cannot be blinded to the intervention or the clinicians responsible for patient care, only data collection and analysis will be blinded [23]. Figure 1 shows the trial flow chart.

### Participant selection

The inclusion criteria are as follows: 1) age range, 18–65 years; 2) diagnosis of gastric cancer and eligible for laparoscopic radical gastrectomy; 3) no chemotherapy, radiotherapy, and targeted therapy before surgery; 4) Nutritional Risk screening 2002 (NRS2002) ≤ 5; and 5) provide informed consent.

The exclusion criteria are as follows: 1) concurrent cancer; 2) remnant gastric cancer; 3) complications (bleeding, perforation, or obstruction); 4) emergency surgery.

### Treatment protocols

This is a confirmatory, single-site, non-inferiority RCT to assess the safety and feasibility of EOF after TLRG compared to DOF.

All eligible patients with gastric cancer will be randomly assigned in a 1:1 allocation ratio to the EOF or DOF group. Participants in both groups will undergo similar peri-operative procedures, with the exception of different oral feeding beginning times. All study data will be stored in an Excel 2007 file, which will be monitored by a nurse who is not involved in this study.

### Peri-operative procedures

Before surgery, gastroscopies, endoscopic biopsies, and computed tomography scans will be performed to confirm the tumor size and location, and patients with organic metastases will be excluded based on assessment by two experienced pathologists. The ERAS guidelines will be followed and all participants will receive pre-operative education, pre-emptive and multimodal analgesia, early ambulation, and laparoscopic radical gastrectomy as part of the peri-operative treatment.

Laparoscopic radical gastrectomies will be performed by the same experienced surgical teams, who have carried out this procedure with an annual caseload of approximately 100 gastric cancer patients. The main anastomosis will be completed laparoscopically, and the abdominal incision will be < 10 cm. After the gastrectomy, Roux-en-Y, Billroth II, or Billroth I reconstruction will be performed in distal gastrectomies and Roux-en-Y esophagojejunostomy in total gastrectomies. Considering the possibility of anastomotic leakage, a peri-anastomotic drain will be placed near the anastomosis after surgery. In most cases, the nasogastric tube will be removed on POD1 and use of a nasojejunal tube will be avoided.

### Intervention protocols

The intervention group will follow the ERAS program and ESPEN guidelines after gastrectomy with respect to enteral nutrition. EOF will be initiated in the form of a clear liquid diet within 24 h after surgery, while a clear liquid diet will be initiated between POD4 and POD6 in the DOF group. In both groups, 1440 mL/day of parenteral nutrition (fat emulsion, amino acids, and glucose injection) or other parenteral nutrition products will be used from POD1–3.

Patients allocated to the EOF group will receive 50–500 mL of 10% glucose injection or other liquid, such as hot pure water on POD1 (within 24 h), followed by 50–500 mL of enteral nutritional suspension on POD2, and > 1000 mL from POD3–6 as tolerated, whereas the participants randomized to the DOF group (control group) will receive the same oral feeding content as described above during this trial (starting on POD4). The only difference between the intervention and control arms will be the oral feeding start time after surgery. Thus, the DOF group will fast for 3 days and receive 50–500 mL of a 10% glucose injection on POD4 and > 1000 mL of enteral nutritional suspension on POD6.

The intervention was planned to POD6. A nutritionist will supervise the oral feeding during the trial using the diet principle of smaller and more frequent intake according to individual tolerance. Adequate caloric intake will be calculated using the Harris-Benedict formula (25–35 kcal/kg/day). An investigator will be assigned to record the clinical observation data.

Only when the gut is intolerant (unable to meet 60% of the daily requirements on POD4) or there is a suspicion of anastomotic leakage, will total parenteral nutrition be considered. Discharge criteria are defined as maintaining normal temperature for 3 days, ambulation, and ability to tolerate oral liquids ad libitum.

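### On the protocol's own feeding schedule no DOF patient can reach the POD4 intake level that separates tolerance from intolerance, so the rule for considering total parenteral nutrition contradicts the schedule

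*Protocol article*

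**What the plan says.** All the conflicting statements stand in the protocol article under Intervention protocols.

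- The rule: "Only when the gut is intolerant (unable to meet 60% of the daily requirements on POD4) or there is a suspicion of anastomotic leakage". No arm is named. The consequence is left to judgement, since the sentence ends "will total parenteral nutrition be considered".
- The requirement: "Adequate caloric intake will be calculated using the Harris-Benedict formula (25–35 kcal/kg/day").
- DOF intake on POD4: "the DOF group will fast for 3 days and receive 50–500 mL of a 10% glucose injection on POD4". The section also allows a later start: "a clear liquid diet will be initiated between POD4 and POD6 in the DOF group".
- EOF intake, after glucose or another liquid on POD1: "followed by 50–500 mL of enteral nutritional suspension on POD2, and > 1000 mL from POD3–6 as tolerated".
- Scheduled parenteral nutrition, in both groups: "or other parenteral nutrition products will be used from POD1–3".
- The claim about the contrast: "The only difference between the intervention and control arms will be the oral feeding start time after surgery".

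Elsewhere, the Randomization procedure section says that patients and treating clinicians cannot be blinded. Study endpoints lists 30-day complications, length of stay and hospitalization costs as secondary endpoints. The Background says that intake volume is not limited in either group.

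**The concern.** A criterion for gut intolerance should depend on how the gut behaves. Here POD4 is the first feeding day in one arm and the fourth in the other, and the DOF schedule for that day supplies only a small amount of glucose solution. A DOF patient who takes everything offered still falls short of the level, because of the schedule and not because of the gut.

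The shortfall opens the door to a co-treatment, and the clinicians who decide on it know the arm. If they act on the rule as written, parenteral support after POD3 could be more frequent in DOF. Part of any difference in cost, stay or complications might then come from that support and not from the timing of oral feeding. Cost is the most directly exposed.

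**Working it through.** The protocol does not convert its 60% level into kcal, so there is no stated figure to reproduce. The check is whether the POD4 schedule can reach that level in each arm.

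**Inputs from Intervention protocols:** level 60%; requirement 25–35 kcal/kg/day; DOF on POD4, 50–500 mL of 10% glucose; EOF on POD4, more than 1000 mL of suspension as tolerated; scheduled parenteral nutrition on POD1–3 only.

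**Assumptions, not in the documents:** glucose energy 3.4–4.0 kcal/g; body weight 40–80 kg; energy density of the suspension 0.75–1.5 kcal/mL.

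**1. DOF intake on POD4** = volume × 0.10 g/mL × kcal/g.
- 50 mL: 5 g, 17–20 kcal.
- 500 mL: 50 g, 170–200 kcal.
- Start on POD5 or POD6: 0 kcal on POD4.

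**2. The 60% level** = 0.60 × weight × (25 to 35).
- 40 kg: 600–840 kcal.
- 60 kg: 900–1260 kcal.
- 80 kg: 1200–1680 kcal.

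**3. DOF maximum as a share of the full requirement** (60% is needed).
- 40 kg: 170/1400 = 12% to 200/1000 = 20%.
- 60 kg: 170/2100 = 8% to 200/1500 = 13%.
- 80 kg: 170/2800 = 6% to 200/2000 = 10%.

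**4. Could any assumption rescue it?** With the most favourable values, 200 kcal reaches 60% only at 200/(0.60 × 25) = 13.3 kg or less. Put without body weight, the daily requirement would have to be 200/0.60 = 333 kcal or less. Neither is possible in the eligible adults aged 18–65.

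**5. Could unlimited volume rescue it?** At 60 kg the volume of 10% glucose needed is 900/(0.10 × 4.0) = 2250 mL to 1260/(0.10 × 3.4) = 3706 mL, against the 500 mL scheduled.

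**6. EOF on POD4 with 1000 mL.** The heaviest patient who reaches 60% weighs 1000 × density/(0.60 × kcal/kg).
- 0.75 kcal/mL: 36–50 kg.
- 1.0 kcal/mL: 48–67 kg.
- 1.5 kcal/mL: 71–100 kg.

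At 60 kg and 1.0 kcal/mL, 1000 mL supplies 1000/2100 = 48% to 1000/1500 = 67% of the requirement.

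The level is therefore out of reach for every DOF patient on schedule, and within reach for some or most EOF patients depending on weight and product.

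**The case against.** The strongest reply is that the rule restricts and does not trigger. It says when total parenteral nutrition may be considered and leaves the decision to judgement. This stands. A reader might infer that DOF patients will automatically receive total parenteral nutrition, but the text supports only that they become eligible for it to be considered.

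A second reply is that being unable to reach an intake means failing when it is offered, so a patient deliberately given a small volume has not failed. The Statistical analysis section also speaks of intolerance only in connection with early feeding. On that reading POD4 is a checkpoint for EOF alone. This is plausible, but the rule does not say so, and a rule confined to one arm would itself be a second difference between the arms. The reading supports clarifying the rule; it does not remove the conflict.

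A third reply is that the separation is not clean, because EOF intake is as tolerated and some EOF patients will also miss 60%. Step 6 of the working confirms this.

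A fourth is that later parenteral support may belong to the delayed-feeding strategy under intention-to-treat. That is a legitimate estimand, but it is not the contrast that the sentence on the only difference describes.

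Three further inferences are tempting and not supported:
- That a comparison of intolerance between arms is spoiled. None is planned; the Statistical analysis section plans only an analysis of factors behind intolerance of early feeding.
- That DOF patients are left without nutritional support on POD4–5. The article is silent on supplemental parenteral nutrition after POD3, and a condensed article may leave such detail to the full protocol.
- That the leakage comparison is biased. Nothing in the documents shows this.

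**Conclusion.** The contradiction holds as written. The POD4 level is unreachable in DOF: at most 20% of the requirement is supplied at an assumed 40 kg and 13% at an assumed 60 kg, against the 60% needed, and nothing is taken by mouth if feeding starts later. This holds for any adult weight, any value in 25–35 kcal/kg/day and either glucose energy value. That the level is reachable in EOF depends on the assumed density of the suspension and on tolerance.

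The consequence is conditional. Applied literally, the rule makes all DOF patients eligible for total parenteral nutrition to be considered, so its use after POD3 could differ by arm. How often clinicians would act on it cannot be derived from the documents, and no size can be given for any bias in cost, stay or complications. The point concerns the interpretation of those secondary endpoints and the accuracy of the sentence on the only difference. It is worth correcting, but it does not undermine the primary analysis.

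**What to change.** The clinical team should reconcile the POD4 rule, the DOF feeding schedule (including the POD4–6 start window) and the POD1–3 parenteral plan, and state to whom the rule applies. No clinical rule is proposed here.

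On the statistical side, record for each patient the number of days of parenteral nutrition after POD3, and report it by arm beside cost, length of stay and complications. The sentence that only feeding start time differs should then be kept or qualified to match the reconciled text.

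The cost is small: a clarification, plus slight extra recording and reporting. The Abstract already plans to record total and oral nutritional intake, although Data collection and schedule does not list parenteral nutrition days. With 102 of 200 patients recruited at submission, the clarified text could apply to up to 98 more. For those already treated, the variable is available only as far as the intake data captured it.

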### Data collection and schedule

Once informed consent is signed, baseline data, such as age, gender, body mass index (BMI), and complications, will be collected by a clinical research assistant. The laboratory data (total serum protein, serum albumin, and blood glucose) will also be tested pre-operatively and during hospitalization to monitor the patients’ nutritional status. A specified operator will record the details of surgical procedures, such as the operative approach, the location of the tumor, lymph node metastasis, and pathologic TNM stage.

From POD1–6, clinical observation data (anastomotic leakage, the time of first flatus and defecation, NRS pain score, post-operative hospital stay, and complications) will also be recorded daily to evaluate the post-operative recovery by an investigator. The clinicians will be responsible for patient care and will not be involved in data collection.

The contact information and address of patients will be confirmed before hospital discharge. Two follow-up visits will be carried out in the outpatient clinic or via telephone 4 and 12 weeks after hospital discharge, focusing on tolerance of the diet and any discomfort. The details of the schedule are shown in Fig. 2.

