### Study endpoints

The primary endpoint will be the percentage incidence of anastomotic leakage after TLRG. We will determine whether or not EOF at POD1 is non-inferior in terms of the occurrence of post-operative fistulas, including anastomotic leakage. Anastomotic leakage will be defined as the breakdown of the connection and subsequent leakage of digestive system fluid from a surgical anastomosis of digestive system structures. If anastomotic leakage is clinically suspected post-operatively, digestive tract radiography will be performed to diagnose the leak. Usually, sufficient abdominal drainage is the most effective treatment.

The secondary endpoints are post-operative recovery and nutritional status, as follows: (1) post-operative complications (n) at 30 days according to the Clavien Dindo classification, which include incisional infection, abdominal abscess, intraperitoneal hemorrhage, anastomotic bleeding, postoperative intestinal obstruction, pancreatitis, pulmonary complications, and others organ complications; (2) the time of first flatus and defecation (day); (3) post-operative length of stay (day); and (4) hospitalization costs (Yuan).

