### Statistical analysis

The intention-to-treat principle will be applied in all analyses with an assumed drop-out rate. Normally distributed continuous variables will be described as the mean with corresponding SDs, and non-normally distributed or categorical variables will be described as medians with the corresponding range or percentages and frequencies. Normally or non-normally distributed continuous data will be compared by Student’s *t*-test or the Mann–Whitney U test, and the chi-square test and Fisher’s exact test will be used to compare categorical variables, as indicated. With the exception of the primary outcome, secondary outcomes, such as post-operative complications, time of first flatus and defecation, and post-operative length of stay, will also be compared. The potential risk factors for intolerance of EOF and post-operative complications will be identified using a multivariate analysis. A blinded statistician will analyze all of the data using a two-sided *P* value < 0.05 to represent statistical significance.

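### Nutritional status is announced as a secondary endpoint but given no measure, and the only stated method for continuous data makes no adjustment for the pre-operative value

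*Protocol article*

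**What the plan says.** The Study endpoints section opens its list with "The secondary endpoints are post-operative recovery and nutritional status, as follows". The four items that follow are complications, bowel recovery (flatus and stool), length of stay, and costs. None is a nutritional measure.

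The Data collection and schedule section says: "The laboratory data (total serum protein, serum albumin, and blood glucose) will also be tested pre-operatively and during hospitalization". It gives the purpose as monitoring nutritional status, the same term that heads the endpoint list. The text names no analysis day, and the schedule figure is not shown.

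The Statistical analysis section gives one general rule: "Normally or non-normally distributed continuous data will be compared by" a t-test or a Mann-Whitney test, according to distribution. It then says that "secondary outcomes, such as post-operative complications, time of first flatus and defecation, and post-operative length of stay, will also be compared". No laboratory value is named there. The section's only multivariable model serves another purpose: "The potential risk factors for intolerance of EOF and post-operative complications will be identified using a multivariate analysis".

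**The concern.** There are two linked gaps. First, an endpoint domain is announced and then left empty. A reader of the results could not tell which marker, on which day, was meant to represent nutritional status, and the choice could be made after the data are seen.

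Second, if albumin or total protein fills that gap, each is a continuous outcome with its own pre-operative measurement, which would be expected to predict the post-operative value. The stated tests take no account of it when post-operative values are compared. The confidence interval is then wider than it need be, and any chance imbalance before surgery stays in the estimate. At stake is the precision of one secondary comparison.

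**Working it through.** **Figure in the plan.** The article gives no sample size, power, standard deviation or correlation for nutritional status, so there is no figure to reproduce. The only inputs taken from it are the group sizes in the Sample size estimate section, which were set for leakage: 80 per arm evaluable and 100 per arm recruited (80 / (1 − 0.20) = 100).

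**Assumptions.** The correlation r between the pre-operative and post-operative value of a marker is assumed to be 0.3, 0.5 or 0.7. Effects are in units of the post-operative SD, with equal SDs before and after surgery. The test is two-sided at 0.05 with 80% power, using normal approximations. The comparison is with the t-test; the formulas do not carry over exactly to the rank test.

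**Variance relative to post-operative values alone**

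- Post-operative values only: 1
- ANCOVA: 1 − r²
- Change from baseline: 2(1 − r)

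| r | ANCOVA | Reduction by ANCOVA | Equivalent sample size, 1/(1 − r²) | Change score |
|---|---|---|---|---|
| 0.3 | 1 − 0.09 = 0.91 | 9% | 1.10 times | 1.40 |
| 0.5 | 1 − 0.25 = 0.75 | 25% | 1.33 times | 1.00 |
| 0.7 | 1 − 0.49 = 0.51 | 49% | 1.96 times | 0.60 |

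A change-score test does not make the point moot. The difference between the two factors is 2(1 − r) − (1 − r²) = (1 − r)², which is never negative, so ANCOVA is never the less efficient of the two. At r = 0.3 the change score is worse than ignoring the baseline, and at r = 0.5 it gains nothing.

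**Detectable difference**, (1.960 + 0.842) × √(2/n) × √(variance factor):

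| n per arm | Post-operative only | ANCOVA, r = 0.3 / 0.5 / 0.7 | Change, r = 0.3 / 0.5 / 0.7 |
|---|---|---|---|
| 80 | 0.443 SD | 0.423 / 0.384 / 0.316 SD | 0.524 / 0.443 / 0.343 SD |
| 100 | 0.396 SD | 0.378 / 0.343 / 0.283 SD | 0.469 / 0.396 / 0.307 SD |

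**Power** for an assumed difference of 0.4 SD at 80 per arm is 72% with post-operative values only. With ANCOVA it is 76%, 83% and 94% at r = 0.3, 0.5 and 0.7.

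**The case against.** The strongest reply is that no laboratory comparison between arms is specified at all. The tests are described as monitoring, no marker is in the endpoint list or the analysis section, and covariate adjustment of a secondary outcome is commonly left to an analysis plan that is not shown here. This stands in part. The absence of ANCOVA would not be a finding by itself. But the article does fix a general method for continuous data, and its list of secondary endpoints names a domain that no item covers. That mismatch is in the text itself.

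A reader might go further and infer that the plan discards the pre-operative values. The article does not say so. It leaves open whether post-operative values or changes are compared, and a test on change would use the baseline.

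A reader might also infer that the laboratory values are the only nutritional data. They are not: the abstract says that nutritional intake, total and by mouth, is also recorded. Albumin and total protein are proposed because they have a pre-operative value and are collected expressly for nutritional status. That intake is also available makes it more necessary to say which measure is the endpoint.

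Nor do the documents support a charge of bias. Under randomisation the unadjusted comparison is valid, and only precision is lost. At a correlation of 0.3 the gain from adjustment is small.

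**Conclusion.** The point holds as a minor, inexpensive improvement. Nutritional status is named as a secondary endpoint without a measure or time point, and the one stated method for continuous data does not adjust for a baseline that is already collected. The definition gap is certain from the text. The gain from adjustment is conditional: a 9% to 49% reduction in variance for r between 0.3 and 0.7, where r is assumed and does not appear in the article. The non-inferiority comparison of leakage does not depend on this.

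**What to change.** - **Study endpoints.** Add a fifth item: serum albumin and total protein at one fixed post-operative day, the same in both arms and already in the trial's schedule. The schedule figure is not shown, so the day must be chosen from it; this assumes that it contains a common day. Do not use the last value before discharge. Discharge requires tolerance of oral liquids, the arms start oral feeding on different days, and length of stay is itself an outcome, so the measurement day could differ by arm. Adjusting for the pre-operative value would not remove that difference.
- **Statistical analysis.** Add that each marker is compared by ANCOVA with the pre-operative value of the same marker as covariate, reporting the adjusted mean difference with its 95% confidence interval.

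The cost is one line in each section, with no new data and no change to the primary analysis. The Trial status section reports 102 of the planned 200 patients recruited at submission. The change should be documented before any comparison of these markers by arm has been seen.
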